### Anthropometric parameters, AGE measurement and health related questionnaire

Height and weight will be measured using a stadiometer (up to 2 meters) and a weighing scale (200 kilograms). Weight will be measured without shoes and with light clothes in the morning. Blood pressure will be measured using a sphygmomanometer. The blood pressure will be measured at the right arm whilst the patient is sitting for at least 5 minutes. Tape-measurements will be performed for waist and hip circumferences. Body Mass Index (BMI) will be calculated by dividing weight through the square of height. Waist to hip ratio will be calculated by the formula: waist circumference/hip circumference. The AGE accumulation in the skin will be measured using an AGE reader (Diagnoptics Technologies B.V., Groningen, The Netherlands). This is a non-invasively device that can assess the tissue accumulation of AGEs using fluorescence of ultraviolet light in human tissue. The forearm is put on the machine and the concentration is assessed by ultraviolet light. This procedure takes 3 minutes and will be done at baseline and at the final visit.

SF-36 health survey will be used to assess health-related quality of life on emotional and physical wellbeing. The patients will receive the questionnaire at baseline and at the end of the trial with a self-addressed envelope.

### Blood collection

Venous blood sampling will be drawn at 0, 3 and 6 months by registered staff nurses using a sterile vacutainer needle between 8.00 and 9.30 am. All participants will be asked to fast overnight for at least 8 hours before blood collection. Blood serum will be used for the analysis of HbA_1c_, C-peptide, fasting insulin, calcium, phosphate, albumin, PTH, liver enzymes, lipid profile, C-reactive protein, TSH, platelets count, leukocytes and hemoglobin and 25 (OH) D ((iSYS automated immunoanalyser (IDS GmbH, Frankfurt, Germany)). The total 25-OH vitamin D assay detects 25-OH VD3 and 25-OH VD2, both with a specificity of 100%. The quality of the test is controlled by applying Westgard QC-rules on 3 different QC-samples [33]. The accepted interassay coefficients of variation are <10% for all 3 QC-samples (low, medium and high level). TSH and intact-PTH will be determined on a Beckman Coulter UniCel DxI 600 Synchron Access immunoanalyser (Beckman Coulter Nederland B.V., Mijdrecht, the Netherlands). Calcium, phosphate, glucose, albumin, liver enzymes, C-reactive protein and lipid profiles will be determined on a Beckman Coulter UniCel DxC 860i Synchron Clinical system chemistry analyzer. C-peptide and insulin will be determined on Siemens Immulite XPi automated immunoanalyser (Siemens Medical Solutions Diagnostics B.V., Breda, the Netherlands). HbA_1c_ will be measured on a HA-8180 automated HPLC system Menarini (Florence, Italy). The total white blood cell count, platelets count and haemoglobin content will be performed with an automated Sysmex XE-2100 blood cell counter (Sysmex Coorperation, Kobe, Japan).

Fasting blood glucose will be measured in blood plasma. Homeostasis model assessment of insulin resistance (HOMA-IR), calculated by fasting glucose (mmol/l) x fasting insulin (IU/ml)/22,5 and QUICKI, calculated by 1/log (fasting insulin (IU/ml)) + log (fasting glucose (mg/dl)), will be used to evaluate insulin resistance. Pancreatic beta-cell function will be assessed through the HOMA-B, calculated by (20 x fasting insulin (IU/ml))/(fasting glucose (mmol/l) – 3,5). All assays will be performed according to the manufacturer’s instructions and carried out by the central chemical laboratory of the Medical Centre Alkmaar, the Netherlands. This laboratory is a certified CCK laboratory. Aliquots of serum and plasma will be stored at -70/80’C for future research questions.

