### Outcomes

The primary outcome of the study is HbA_1c_. Secondary outcomes are insulin resistance and beta-cell function measured by the homeostasis model of assessments (HOMA) and quantitative insulin sensitivity check index (QUICKI). Further secondary outcomes include the alteration of serum 25 (OH) D over time, blood pressure, lipid profile, parathyroid hormone, calcium, thyroid function, AGE accumulation in the skin, safety profile of vitamin D supplementation, urine analysis for microalbuminuria, and quality of life assessed by The Short Form (SF-36) Health Survey questionnaire.

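### The printed QUICKI formula has no bracket around its sum, so this insulin sensitivity index rises with fasting glucose; the insulin unit in all three indices needs verifying

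*Protocol article*

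**What the plan says.** The Outcomes section of the protocol article reads: "Secondary outcomes are insulin resistance and beta-cell function measured by the homeostasis model of assessments (HOMA) and quantitative insulin sensitivity check index (QUICKI". Insulin resistance is also part of objective i at the end of the Background.

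The formulas appear only under Blood collection:

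- HOMA-IR: "calculated by fasting glucose (mmol/l) x fasting insulin (IU/ml)/22,5".
- QUICKI: "QUICKI, calculated by 1/log (fasting insulin (IU/ml)) + log (fasting glucose (mg/dl)), will be used to evaluate insulin resistance".
- HOMA-B: "calculated by (20 x fasting insulin (IU/ml))/(fasting glucose (mmol/l) – 3,5", where the denominator is properly enclosed.

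All three give insulin in IU/ml. No other section restates or corrects the QUICKI formula or the insulin unit, and the base of the logarithm is not given.

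**The concern.** Under the ordinary order of operations the printed QUICKI is the reciprocal of log insulin, plus log glucose. The glucose term therefore has the wrong sign for an index of insulin sensitivity. At a given insulin level, a patient whose fasting glucose fell during the trial would be scored as having become less sensitive.

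The formula is the operative definition of an outcome, so someone programming from the article could code it literally. The same paragraph encloses the HOMA-B terms correctly, which gives that person some reason to take the QUICKI brackets at face value.

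The insulin unit is a second, separate question. IU/ml does not fit the usual scaling of the HOMA constants, and inside a logarithm the choice of unit is not a mere rescaling.

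**Working it through.** **Inputs.** The three formulas are from Blood collection. The article gives no worked value for any index, so there is no stated figure to reproduce. The patient values are assumptions: fasting insulin 10 micro-IU/ml (0.00001 IU/ml), with a range of 5 to 30; glucose 7 and 10 mmol/l, which are 126 and 180 mg/dl (factor 18.016), with a range of 5 to 10 mmol/l.

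**Step 1: what direction the index should have.** With the bracket, the denominator is log(insulin) + log(glucose) = log(insulin × glucose). HOMA-IR as printed is the same product divided by 22.5. Bracketed QUICKI therefore falls whenever HOMA-IR rises, as a sensitivity index should against a resistance index.

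**Step 2: the numbers, log base 10, insulin 10 micro-IU/ml.** log10(126) = 2.100; log10(180) = 2.255; log10(10) = 1; log10(0.00001) = −5.

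| Version | Glucose 126 mg/dl | Glucose 180 mg/dl | Direction |
|---|---|---|---|
| As printed, IU/ml | 1/(−5) + 2.100 = 1.90 | 1/(−5) + 2.255 = 2.06 | rises |
| No bracket, micro-IU/ml | 1/1 + 2.100 = 3.10 | 1/1 + 2.255 = 3.26 | rises |
| Bracket, micro-IU/ml | 1/(1 + 2.100) = 0.323 | 1/(1 + 2.255) = 0.307 | falls |
| Bracket, IU/ml | 1/(−5 + 2.100) = −0.345 | 1/(−5 + 2.255) = −0.364 | falls, but negative |

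The wrong direction comes from the missing bracket alone. Natural logarithms give the same result: without the bracket, going from 7 to 10 mmol/l moves the index from 4.750 to 5.107 in IU/ml and from 5.271 to 5.628 in micro-IU/ml.

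**Step 3: how far the ranking of patients changes.** At 7 mmol/l, moving insulin from 5 to 30 micro-IU/ml changes the unbracketed index from 1.912 to 1.880 if coded in IU/ml (0.032), and from 3.531 to 2.778 if coded in micro-IU/ml (0.753). Doubling glucose from 5 to 10 mmol/l adds log10(2) = 0.301 in both cases. Glucose therefore dominates in IU/ml, and insulin dominates in micro-IU/ml.

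A simulation shows the same. It assumed log-normal insulin (median 12 micro-IU/ml, log-SD 0.6) and log-normal glucose (median 7.5 mmol/l, log-SD 0.17), with a correlation of 0 or 0.3 between their logarithms. Spearman correlations with HOMA-IR were:

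- bracketed, micro-IU/ml: −1.0;
- unbracketed, IU/ml as printed: 0.12 and 0.38 (and 0.99 with glucose itself);
- unbracketed, micro-IU/ml: −0.81 and −0.82.

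**Step 4: the unit.** Take glucose 7 mmol/l and insulin 10 micro-IU/ml. HOMA-IR = 7 × 10/22.5 = 3.11 and HOMA-B = 20 × 10/(7 − 3.5) = 57.1. With insulin entered as 0.00001 IU/ml they are 0.00000311 and 0.0000571. The factor is the same for every patient, so t-tests, rank tests and p-values between arms do not change.

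In bracketed QUICKI, IU/ml subtracts 6 from the denominator. Over the assumed range the denominator in micro-IU/ml is at most log10(30) + log10(180) = 1.477 + 2.255 = 3.73, so every value becomes negative. The order of patients is kept, but the spacing is not, so comparisons of means change.

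**The case against.** The strongest reply is that this is a misprint with an obvious intention. The Outcomes section names the index in full as one of insulin sensitivity. HOMA-IR comes from the same samples and has the right structure, so a faulty QUICKI could be noticed against it. Neither the analysis code nor a statistical analysis plan is shown, and nothing indicates that the misprint would reach the analysis. All of this stands and limits the weight of the point. It does not remove it, because the article chose to state the formula, states it wrongly, and corrects it nowhere.

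On the unit, the reply is stronger still. No micro sign appears anywhere in the text, and the storage temperature in the same section has an apostrophe where a degree sign belongs. A symbol lost in typesetting or text conversion is plausible. Other special characters do survive (α, γ, ≥), so an author's slip cannot be excluded either. The unit can only be raised as something to verify.

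A reader might infer three stronger things that the article does not support:

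- That the HOMA results would be invalid because they are a million-fold too small. The factor is constant, affects reported values only, and would be noticed at once.
- That mixing mg/dl in QUICKI with mmol/l in HOMA is an error. Each formula labels its glucose unit, and the corrected QUICKI keeps mg/dl.
- That the printed QUICKI simply reverses HOMA-IR. Only the glucose term has the wrong sign. With insulin in micro-IU/ml the unbracketed index still correlates at about −0.8 with HOMA-IR; the positive correlation arises only with IU/ml taken literally.

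**Conclusion.** The QUICKI definition is wrong as written: without the bracket it rises with fasting glucose under either insulin unit and either log base. At the assumed insulin level, the rise from 126 to 180 mg/dl adds about 0.155 (log10 scale), where the intended index falls by about 0.016 (0.323 − 0.307). The direction rests only on the printed expression and the name of the index; the sizes rest on the assumed insulin and glucose values and, for the rank correlations, on the assumed distributions.

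The insulin unit is unconfirmed. That the constants 22.5 and 20 are scaled for micro-IU/ml is the usual convention and is not stated in the article.

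The reach is limited. Insulin resistance and beta-cell function are secondary outcomes, and the Abstract lists insulin resistance after blood pressure, anthropometry and lipids. The primary HbA1c comparison and the sample size do not use these formulas.

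**What to change.** Define QUICKI = 1/[log10(fasting insulin, micro-IU/ml) + log10(fasting glucose, mg/dl)], with the bracket and the log base explicit.

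Check the insulin unit in all three formulas against the original document. If it reads micro-IU/ml there, nothing more is needed. If it really reads IU/ml, change it to micro-IU/ml in HOMA-IR, QUICKI and HOMA-B. The glucose units can stay as they are.

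The cost is one corrected formula and possibly one unit label in three places. No data, visit or sample size changes. The Trial status section says recruitment is still under way, so the correction can be made before analysis.

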### Adverse events

All serious adverse events (SAEs) will be reported through the web portal *ToetsingOnline* to the accredited Medical Ethics Committee that approved the protocol, within 15 days after the sponsor has first knowledge of the serious adverse reaction. SAEs that result in death or are life threatening episodes should be reported expedited. The expedited reporting will occur not later than 7 days after the responsible investigator has first knowledge of the adverse reaction. This is for a preliminary report with another 8 days for completion of the report.

## Discussion

The main purpose of this study is to measure the effect of vitamin D supplementation on glycaemic control and health related quality of life in patients with T2DM. There is widespread interest in the potential causal role of vitamin D on the pathogenesis and progression of T2DM. We hope this study will give new insight into this causality. Until now conflicting results are seen in observational studies and the few clinical trials performed, which could not confirm a causal association [7-14]. Factors for the lack of effect found in these studies includes: short trial duration, relatively low doses of vitamin D supplementation whether or not combined with calcium supplements, and heterogeneous study populations.

This trial has several strengths: the study sample size allows us to perform a subgroup analysis of vitamin D deficient patients. Taken into account that only in vitamin D deficient patients an effect of vitamin D supplementation on glycaemic control will be found, we chose to recruit double the number of participants as calculated with the power estimation, hypothesizing that 50% of the included patients will be vitamin D deficient (serum 25 (OH) D < 50 nmol/l). Secondary, the relatively high dose chosen for intervention and the duration of the trial are strengths of our study. The dose of vitamin D supplementation of 50,000 IU of vitamin D per month (daily equivalent ~1667 IU) is based on the recommendations of the Institute of Medicine and on the study done by van Groningen et al. [31,34]. In this latter study, performed in the Netherlands, it was demonstrated that a cumulative dose of 100,000 IU given in 2 months increases the serum 25 (OH) D meanly with 29 nmol/l. Assuming that the mean serum 25 (OH) D in our study population will be around 50 nmol/l at baseline, the serum 25 (OH) D should be raising to a sufficient status (≥75 nmol/l) in two months. To measure a difference in HbA_1c_ level we hypothesize that the maximal effect will be seen at least at six months, regarding the fact that the red blood cells circulate about 100 days in the blood and HbA_1c_ levels takes around six weeks to change. Furthermore, this is the first study examining the association between vitamin D status and skin autofluorescence value as well as the effect on skin AGEs after vitamin D supplementation. For this secondary outcome the duration of our trial will be a limitation, regarding the stability and long half-life of skin AGEs with could be the cause to find no effect of vitamin D supplementation on skin AGEs.

The results of this trial should provide more insight into the potential causal association between vitamin D status and glycaemic control in patients with T2DM.

### Trial status

This study is in the process of participant recruitment.

## Abbreviations

1,25(OH)2D: 1,25-dihydroxyvitamin D; 25(OH)D: 25-hydroxyvitamin D; 1α-OHase: 1-α-hydroxylase; AGE: Advanced glycation end products; ANOVA: Analysis of variance; BMI: Body mass index; HbA_1c_: The standard measure glycaemic control, measuring glycaemic control over the last six to eight weeks; HOMA: Homeostatic model assessment; IU: International units; PTH: Parathyroid hormone; QUICKI: Quantitative insulin sensitivity check index; SF-36: Short form 36 of health survey; VDR: Vitamin D receptor.
